## Abstract

**Introduction:**

Retention in HIV care is necessary to achieve adherence to antiretroviral therapy, viral load suppression, and optimal health outcomes. There is no standard definition for retention in HIV care, which compromises consistent and reliable reporting and comparison of retention across facilities, jurisdictions, and studies.

**Objective:**

The objective of this study is to explore how stakeholders involved in HIV care define retention in HIV care and their preferences on measuring retention.

**Methods:**

We will use an exploratory sequential mixed methods design involving HIV stakeholder groups such as people living with HIV, people involved in providing care for PLHIV, and people involved in decision-making about PLHIV. In the qualitative phase of the study, we will conduct 20–25 in-depth interviews to collect the perspectives of HIV stakeholders on using their preferred retention measures. The findings from the qualitative phase will inform the development of survey items for the quantitative phase. Survey participants (n = 385) will be invited to rate the importance of each approach to measuring retention on a seven-point Likert scale. We will merge the qualitative and quantitative findings phase findings to inform a consensus-building framework for a standard definition of retention in care.

**Ethical issues and dissemination:**

This study has received ethics approval from the Hamilton Integrated Research Ethics Board. The findings will be disseminated through peer-reviewed publications, conference presentations, and among stakeholder groups.

**Limitations:**

This study has limitations; we won’t be able to arrive at a standard definition; a Delphi technique amongst the stakeholders will be utilized using the framework to reach a consensus globally accepted definition.

## Introduction

Globally, 38.4 million people are living with HIV, with 1.5 million new infections acquired only in 2021 [1]. In 2015, the United Nations set the Sustainable Development Goals (SDGs), intending to eradicate the HIV epidemic by 2030 [2]. To reach the SDGs, efforts have been made to make free antiretroviral therapy (ART) and quality care accessible for people living with HIV (PLHIV) on a global scale [3, 4]. Despite these efforts, achieving progress towards SDGs remains elusive, given the diverse epidemic challenges countries face, thereby impeding the realization of the overarching goals [2].

To meet the SDGs, it is crucial to retain patients in every stage of the HIV care continuum (initiation of care, adherence to ART and retention in care). Even though ART helps prolong and improve the quality of life of PLHIV, retention in care is essential for ensuring consistent access to ART, monitoring health outcomes, lowering mortality rates, and reducing new HIV infections [5–7]. However, among the entire care continuum, retention in care poses the most significant challenge, with up to 50% of patients not being retained only in USA where accessible and quality care is available [8].

Moreover, the variability in assessing retention across different settings and countries has continued to impede the precise evaluation of retention in care. This hinders the accurate estimation of patients lost to follow-up (LTFU), the evaluation of the effectiveness of HIV treatment programs, and strategic planning of resource allocation [6, 9, 10]. In 2022, the HIV Care Cascade Research Development Team at the CIHR Canadian HIV Trials Network Clinical Care and Management Core Canada collaborated to present HIV care cascade data from local and provincial clinical settings and national cohort studies. However, the findings were limited by the inconsistent HIV care cascade indicator definitions used across different provinces and the variability between the use of nested UNAIDS’s 90-90-90 targets and HIV care cascade indicators [11]. This highlights the need for a standard and globally accepted definition of retention [9, 12–17].

Our recently published review of retention definitions identified that trialists have used several definitions across studies [17]. This heterogeneity in retention measures limits our ability to aggregate data for meta-analysis and to compare findings across studies. Adopting a standardized definition applicable across national and international programmes, diverse settings and partnerships will facilitate accurately quantifying these gaps along the continuum [14]. A reliable and consistent retention measure is crucial to identifying real-world gaps, mapping services and programs, evaluating program performance, making policies, and implementing them to ensure equitable healthcare access [18].

Establishing a standard definition for retention in HIV care encounters challenges due to the need for longitudinal assessment and the diverse socio-economic factors influencing retention in PLHIV [9, 16, 17]. Additionally, the shifts in the treatment paradigm at different times have impeded the consensus on a standardized measure of retention. In 2016, the World Health Organization (WHO) updated ART guidelines to embrace a "treat all" approach, aiming to broaden the reach of HIV treatment, especially to key populations and men, as only 40% of men sought early care. Robust health systems were required to implement "test and treat all," causing delays in lower-middle-income countries until around 2018 [18]. Moreover, to better cater to individuals living with HIV and alleviate post-"treat all" burdens, the Differentiated Service Delivery (DSD) model extended antiretroviral therapy (ART) refill intervals for stable patients to six-month multi-month dispensing (6MMD) [19]). Given the variations in HIV care, resources, societal influences, and economic factors, reaching a consensus on a standardized retention measure without further delay is crucial.

A standard definition must include clinically relevant features and be adequately stable to predict long-term clinical outcomes. The definition should be easy to use, record and report across different settings, healthcare systems, and populations. Arriving at a consensus for a standard definition will require views and perspectives from stakeholders involved in HIV care, including PLHIV [10].

The purpose of this study is to develop a framework of a standard definition of retention in care with consensus from global stakeholders in HIV care, this framework will help us to arrive to a consensus to a standard definition of retention in HIV care. The following research questions guide our study.

### Qualitative research questions

What are the various perspectives of HIV stakeholders engaged in HIV care at national and international levels on measuring retention in HIV care?How do the categories mentioned by the HIV stakeholders help to explain the need for a standard measure of retention in HIV care?

### Quantitative research questions

What components used to define retention are most important to HIV care stakeholders in terms of ease to use, recording, and comparison across different settings, jurisdictions, and studies?

### Mixed method research questions

To what extent and in what ways do qualitative interviews with stakeholders involved in HIV care services contribute to a comprehensive understanding of the various components used to define retention in care?Are the views of HIV stakeholders about measuring retention in their specific context generalizable to HIV stakeholders in a broader context?

## Methods

We will use the pragmatism paradigm as the epistemological framework for our research. Pragmatism is an appropriate approach for our research as we will be examining diverse and complex contexts [20]. Pragmatism will provide us with the flexibility to build variations into techniques and analytic processes, resulting in the production of actionable knowledge. This study is approved by the Hamilton Integrated Research Ethics Board ethics committee (HiREB) at McMaster University (16500).

### Study design

We will conduct an exploratory sequential mixed methods study (QUAL → quan) [18]. The mixed method approach will comprise two phases. In the qualitative phase, we will conduct in-depth interviews building upon retention in care definitions identified in a prior review [10]. In the qualitative phase, we will explore participants’ views on measuring retention with the intent of using this information to develop a survey. In the quantitative phase of the study, the key concepts identified from the qualitative data will be operationalized as quantitative items in a web-based survey. This survey will enable us to generalize the qualitative findings to a larger heterogeneous sample. To achieve complete and comprehensive answers to our research question, qualitative and quantitative findings will be merged for analysis and interpretation, reporting and development of the framework for consensus of the standard definition [18, 19].

### Rationale for design

A mixed-method approach will address the complex and broader question of developing a standard and optimal measure of retention [21]. A mixed-method approach will enable us to use two sampling techniques [22].

Purposeful and probabilistic techniques will ensure data collection in breadth and depth [23]. A qualitative phase of individual interviews will help contextualize and elaborate findings from different settings, populations, and professional backgrounds [24]. The quantitative data will inform us of the magnitude of the relevance of the retention measures [20]. This approach will generate findings that would not otherwise be obtainable when using only qualitative or quantitative methods alone. This mixed-method approach will increase the validity of our interpretations and generate reliable new knowledge [25].

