#### Qualitative phase

The qualitative phase of our study will draw on the principles of qualitative description methodology. This approach is suitable for mixed method study to address clinical questions. This approach is well suited here as this approach will enable us to gain perspectives from participants to understand and describe the phenomenon in terms of literal descriptions and dwell on practical relevance of the information for health care users [27].

We will employ a combination of purposeful sampling techniques, including criterion-based, maximum variation, and snowballing sampling techniques, to seek an equally representative sample in terms of the HIV stakeholders groups (policy, research, practice) and across all WHO geographical regions (African Region, Region of the Americas, South-East Asia Region, European Region, Eastern Mediterranean Region, and Western Pacific Region) [28].

Based on sample size recommendations to reach theoretical sampling, we anticipate performing 25–30 interviews, with 4–5 from each representative group. This sample size seems appropriate to capture information-rich data. This estimation of interview participants is based on a study involving key stakeholders’ perspectives and experiences on defining and identifying health research gaps [26].

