#### Quantitative phase

We will disseminate the surveys to the pre-defined HIV stakeholders groups. We will use the email listservs of organizations working in HIV care, such as the Ontario HIV Treatment Network (OHTN), World Health Organization (WHO) and Joint United Nations Programme on HIV/AIDS (UNAIDS), Global Fund, International AIDS Society (IAS), Kaiser Family Foundation (KFF), The United States President’s Emergency Plan for AIDS (PEPFAR), Canadian Foundation for AIDS Research (CANFAR) and regional WHO groups. Researchers will be identified from publications on retention in care in the CASCADE database (a database of randomized trials on the HIV care cascade) [29]. We will also reach out to existing collaborations and professional associations such as the International AIDS Society (IAS), the Canadian Association for HIV Research (CAHR), and the International Association of Providers of AIDS Care (IAPAC).

To further supplement the recruitment process, we will publicize our study on social media platforms like Twitter and LinkedIn. Patients will be recruited and identified from online patient support groups and organizations serving those patients, such as REALIZE, POZ Community Forum [28]. We will submit an amendment to HiREB regarding any changes in recruitment methods based on guidance of the organizations.

We will disseminate the survey online in the stakeholders’ groups. If response rates are lower than our calculated sample size, we will use a snowballing approach to include responses from participants interested in this topic [30].

We will use a proportional quota sampling method to achieve a diverse and representative sample of participants. We will divide the sample into our pre-defined three strata (policy, health research, and practice) so every HIV stakeholder group is equally represented [31]. People who belong to more than one group will be asked to declare the group they primarily identify with. We will obtain a pre-determined sample population of 385 based on the formula for proportions for a survey, which is the maximum sample size required to estimate a population proportion of 50% with a 95% level of confidence and a 0.5% margin of error. These computations are performed with WINPEPI [32].

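### The rationale calls the sampling probabilistic, but the survey is a quota sample of volunteers, so neither its margin of error nor a population-level generalisation is supported

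*Protocol article*

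**What the plan says.** Under Rationale for design, the article says a mixed-methods approach permits two sampling techniques and then names them: "Purposeful and probabilistic techniques will ensure data collection in breadth and depth".

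The two phases are described under Sampling and sample size:

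- **Interviews (Qualitative phase):** "We will employ a combination of purposeful sampling techniques, including criterion-based, maximum variation, and snowballing sampling techniques".
- **Survey (Quantitative phase):** "We will use a proportional quota sampling method to achieve a diverse and representative sample of participants". The strata are policy, health research and practice. Recruitment runs through organisational listservs, authors found in a trials database, professional associations and online patient groups. In addition, "we will publicize our study on social media platforms like Twitter and LinkedIn". If responses fall short of the target, "we will use a snowballing approach to include responses from participants interested in this topic".

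The same section fixes the survey at 385, using the formula for estimating a population proportion of 50% with 95% confidence and a margin printed as 0.5%.

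On inference, Study design says: "This survey will enable us to generalize the qualitative findings to a larger heterogeneous sample". The second of the Mixed method research questions asks whether stakeholders' views are "generalizable to HIV stakeholders in a broader context". Data integration plans a second joint display to show how the survey result generalises the qualitative context. The limitations paragraph in the abstract does not mention sampling.

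**The concern.** The article gives the survey a property that its own methods section does not deliver. A probability sample needs a defined frame and a known, non-zero chance of selection for each member. The survey has neither: people enter because they saw an invitation and chose to respond, up to a quota.

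The label matters because other statements lean on it. The precision formula, the description of the sample as representative and the generalisability question all read naturally as statements about a population of HIV stakeholders. If the plan is followed as worded, the authors could answer a stated research question at a level the design cannot support.

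It may also touch the one decision rule in the analysis, under which an item counts as important if its mean is 4 or more out of 7. If volunteers rate items differently from stakeholders who did not respond, items near that cut-off could pass or fail because of who answered.

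**Working it through.** **1. Which phase is meant to be probabilistic?** The rationale names two techniques. The interview section takes purposeful sampling for itself, so the other label must belong to the survey.

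**2. Does the survey contain a probability step?** Each route described in the article:

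| Step | Random selection described? |
|---|---|
| Listservs and professional associations | No |
| Authors identified from a trials database | No; they are identified, with no random draw |
| Online patient groups | No |
| Social media publicity | No |
| Quotas by stakeholder group | No; quotas control the mix, not the selection |
| Snowballing (only if responses fall short) | No |

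The conclusion does not depend on the snowballing. Quota sampling with voluntary response is already non-probability.

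**3. Reproducing 385.** Inputs from the article: proportion p = 0.5, 95% confidence (z = 1.95996), margin d.

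n = z² × p(1 − p) / d²

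- d = 0.005, as printed: 0.96036 / 0.000025 = 38,414.6, so 38,415. This does not give 385.
- d = 0.05: 0.96036 / 0.0025 = 384.15, so 385. Exact match.
- Could a finite-population correction rescue 0.5%? Solving for the population size: 385 × (38,414.6 − 1) / (38,414.6 − 385) ≈ 389. A global stakeholder population of 389 is not plausible.

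So 385 is the 5-point figure, and the printed 0.5% appears to be a misprint. The margin at n = 385 is 1.96 × √(0.25 / 385) = 0.0499, or ±5.0 points, about ten times the printed value. The formula assumes simple random sampling.

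**4. How far could the nominal margin mislead?** The documents give no basis for a figure, so everything in this step is an assumed illustration.

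- *Clustering within networks*, margin = 1.96 × √(0.25 × deff / 385): an assumed design effect of 1.5 gives ±6.1 points (effective n = 385 / 1.5 = 257). A design effect of 2.0 gives ±7.1 points (effective n = 385 / 2 = 193).
- *Selection bias in a proportion*, with standard error √(0.25 / 385) = 0.0255: an assumed bias of 5 points would cut the true coverage of a nominal 95% interval to about 50%, and a bias of 10 points to about 2.5%.
- *Selection bias in an item mean*: with an assumed SD of 1.5, the nominal half-width is 1.96 × 1.5 / √385 = 0.15. An assumed upward shift of 0.3 is twice that. Under it, an item whose mean among all stakeholders lay between 4 − 0.3 = 3.7 and 4 would be expected to meet the mean-of-4 rule.

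The bias does not shrink as n grows, so no corrected sample size follows from this point.

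**The case against.** The strongest defence is that little in the study depends on the word. Study design speaks only of generalising to a larger sample, not to a population. The research question on generalisability is posed as a question, so it does not presume the answer. The output is a framework, and the article says that a standard definition is left to a later Delphi exercise. On this view the fault is one misused adjective.

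Part of this stands. The Study design sentence alone would not support the point, and no population estimate directly drives a clinical or policy decision. But the survey section sizes the sample for a population proportion and calls it representative. The research question reaches to a broader context, and the joint display is meant to show generalisation. Together these go beyond one adjective.

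Four stronger readings are tempting, and the article does not support them:

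- *The planned confidence intervals will be too narrow.* The quantitative analysis plans means, medians, frequencies and a cut-off, and no intervals. The margin appears only in the justification of 385.
- *Responses are not tagged by channel, so selection effects cannot be examined.* The article is silent, and an article commonly leaves such set-up to the full protocol.
- *The survey is an open link.* The text says it is disseminated online and that the study is publicised on social media. It does not say how access is controlled.
- *WHO regions are neglected in the survey.* There is no regional quota, but recruitment includes global bodies and regional WHO groups, and demographic information is collected.

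That interested volunteers rate items higher is plausible, but nothing in the article shows it.

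**Conclusion.** The point holds in a limited form. The rationale's description of the sampling contradicts the survey methods in the same article. The figure of 385 is a simple-random-sampling calculation for about ±5 points, not 0.5%, and that margin has no design-based meaning for a quota sample of volunteers. The population-level reading of representative and generalisable is therefore unsupported.

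This rests only on the text and on the reproduction of 385. The size of any selection bias cannot be derived from the article. The margins of ±6.1 to ±7.1 points, the coverage figures and the 0.3-point shift depend on assumed inputs, and the conclusion does not need them.

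The survey remains worth doing. It can describe how a varied set of stakeholders rates the items, overall and by group.

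**What to change.** 1. In Rationale for design, replace probabilistic with non-probability quota sampling.
2. In the survey sample-size paragraph, present 385 as a recruitment target. State that its margin is nominal, about ±5 points, and would hold only under simple random sampling. Correct the printed 0.5%.
3. Answer the generalisability question, and label the second joint display, as descriptive of the survey respondents. List self-selection among the limitations.
4. As a check, record recruitment source by a source question or channel-specific links. Report whether the items meeting the mean-of-4 rule change when snowball and social-media responses are excluded. A forwarded link may be credited to the wrong channel, so read the result with that in mind.

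The first three are wording changes. The fourth needs one survey field or a few links set up before launch, requires no personal identifiers and adds one table. The downside is a more modest generalisability claim.

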### Study timeline

The participants recruitment for the qualitative phase of the study will begin in November 2023 and will continue until March 2024. The qualitative synthesis will occur between April 2024 and June 2024. From the qualitative findings we will develop the survey. The survey will be disseminated from August 2024 till November 2024. The quantitative findings and the integration of the qualitative and quantitative findings will be finalized from December 2024 till February 2025.

### Sampling and sample size

#### Inclusion criteria

For this study, we will recruit HIV stakeholders globally with atleast five years of experience. We will define HIV stakeholders in three main categories based on the evidence to inform policy (policymakers), health research (researchers and funding bodies), and practice (HIV clinicians, clinical guideline developers, public health professionals, and PLHIV) nationally and internationally [26].

The participants recruitment will begin in November 2023, and will continue until June 2024. Participants will be selected if they meet the following inclusion criteria: 1) able to understand both written and spoken English; 2) a minimum age of 18 years of age; 3) are willing to participate in a computer-based online interview about personal experiences with retention in care; and 3) can provide signed informed consent for study participation. Participants will be excluded if they do not participate in the interview or request that their data be withdrawn.

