### Quantitative phase

We will compute the mean (standard deviation) or frequency (percent) based on the survey responses as appropriate for the data.

To determine the level of importance that participants allocate to each item we will compute the mean (SD) or median (quartiles). Only items with a mean of 4 or more out of seven will be considered as important. The mean will inform us which approaches to measuring retention are preferred by the participants. Results will be aggregated by stakeholder groups.

The results will be analyzed using IBM SPSS statistical software [38]. An outline of the study is shown in Fig 1.

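### People living with HIV are a group of their own in the Abstract but are pooled with professionals in the practice stratum, so their number is not secured and a pooled mean can hide their disagreement

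*Protocol article*

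**What the plan says.** The protocol article uses two groupings of stakeholders.

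- **Abstract, Methods:** the study involves "HIV stakeholder groups such as people living with HIV, people involved in providing care for PLHIV, and people involved in decision-making about PLHIV". Patients, providers and decision-makers are listed separately.
- **Sampling and sample size, Inclusion criteria:** "We will define HIV stakeholders in three main categories": policy, health research and practice. The third is "practice (HIV clinicians, clinical guideline developers, public health professionals, and PLHIV", so patients and their clinicians share one category.

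The second grouping governs the design. Interviews seek an "equally representative sample in terms of the HIV stakeholders groups (policy, research, practice". For the survey, the Quantitative phase under Sampling and sample size says: "We will divide the sample into our pre-defined three strata (policy, health research, and practice) so every HIV stakeholder group is equally represented". Someone who fits several groups declares one primary group. The same section recruits patients through online support groups and patient organizations, but attaches no number to that channel.

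In the Analysis section (Quantitative phase), an item counts as important when its mean is at least 4 on the seven-point scale, and "Results will be aggregated by stakeholder groups". The Introduction gives the reason for including patients: "Arriving at a consensus for a standard definition will require views and perspectives from stakeholders involved in HIV care, including PLHIV". The Inclusion criteria also say that "we will recruit HIV stakeholders globally with atleast five years of experience", without saying what experience means for a patient.

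**The concern.** Whether patients and professionals agree on how to measure retention is close to the centre of a study meant to prepare a consensus definition. The Abstract's grouping would show such a disagreement. The Methods' grouping puts both sides in the same stratum. If quotas and reporting follow the Methods, two things are left open.

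1. The practice quota can be met with any mix of clinicians, guideline developers, public health professionals and PLHIV, so the number of PLHIV is left to chance.
2. The mean for practice, and the mean over all respondents, blend the two views. An item that PLHIV rate below the cut-off can be classed as important, and an item that they favour can fail.

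The statement that every stakeholder group is equally represented is then true for the Methods' three strata but not secured for the groups that the Abstract names.

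**Working it through.** **Inputs from the protocol article**
- Survey n = 385, at a proportion of 50% and 95% confidence (Sampling and sample size, Quantitative phase).
- Three strata, equally represented (same section). That section also calls the quotas proportional; equal thirds are taken here, as the equal-representation statement implies.
- Importance cut-off: mean of at least 4 of 7 (Analysis, Quantitative phase).

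**Assumptions, not in the documents:** the PLHIV share of the practice stratum, the example item means, and an SD of 1.5 for a rating.

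**The plan's own figure.** n = 1.96² × 0.25 / d². With d = 0.05 this is 384.1, rounded up to 385. With the printed margin of 0.5% it is 38,415. The figure of 385 therefore belongs to a 5% margin. That is a separate slip and does not affect this point.

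**Stratum size and precision.** 385 / 3 = 128.3. Half-width = 1.96 × √(0.25 / n), so for a whole stratum 1.96 × √(0.25 / 128.3) = 8.7 percentage points.

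**PLHIV inside the practice stratum**

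| Assumed share | PLHIV (of 128.3) | Part of 385 | Half-width, proportion near 50% | Half-width, mean rating (SD 1.5) |
|---|---|---|---|---|
| 10% | about 13 | 3.3% | ±27.4 points | ±0.82 |
| 25% | about 32 | 8.3% | ±17.3 points | ±0.52 |
| 50% | about 64 | 16.7% | ±12.2 points | ±0.37 |

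For comparison, four equal strata hold 385 / 4 = 96.25 each: 1.96 × √(0.25 / 96.25) = ±10.0 points.

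**What pooling does to the cut-off.** With PLHIV share f, the stratum mean is f × (PLHIV mean) + (1 − f) × (mean of the others).
- PLHIV 3.0, others 5.0, f = 0.25: 0.75 + 3.75 = 4.5. The item passes although PLHIV rate it below 4. Since 5 − 2f ≥ 4 for f ≤ 0.5, this holds at every share up to one half.
- PLHIV 5.0, others 3.5, f = 0.25: 1.25 + 2.625 = 3.88. An item that PLHIV favour fails in this stratum. At f = 0.40 the mean is 4.10 and it passes. The turning point is 3.5 + 1.5f = 4, that is f = 1/3.
- Over all respondents, with PLHIV at 1/12 of the sample (a quarter of a third), PLHIV rating an item 1 and everyone else 5: 1/12 + 55/12 = 4.67. The item passes.

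The second example shows that a classification can turn on a share that the plan does not control.

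**The case against.** The strongest reply is that this is mostly labelling. The Abstract's list is introduced as examples and defines no strata, while the Methods use the same three categories throughout, taken from a cited source. The reporting sentence speaks of stakeholder groups, a term that the Abstract also applies to PLHIV, and does not limit tables to three strata. The survey has demographic and professional sections, so a PLHIV breakdown may be possible, and fuller tables may sit in a document not shown. PLHIV can also be heard in the interviews that generate the survey items. The study does not claim to settle the definition, because a Delphi exercise is to follow.

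Much of this limits the point, and some stronger readings should be set aside.
- A reader might infer that PLHIV preferences cannot be seen at all. The documents do not support that: a breakdown remains possible if PLHIV status is recorded. It is only not stated.
- A reader might infer that the practice quota will fill with professionals. Patients have their own channel, and nothing indicates a low yield from it.
- A reader might infer that the experience requirement removes people in their first five years with HIV or in care. The term is undefined for patients, so that effect is not established.
- The margins for a proportion are the plan's sizing basis, not its decision rule. On the mean scale, about 32 PLHIV would give roughly ±0.52 under the assumed SD, which is usable against a cut-off of 4.

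What the reply does not remove is that the article itself fixes the quota structure, claims equal representation on it, and secures no PLHIV number. That is a stated design choice, not a detail left to a fuller document.

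**Conclusion.** The point holds in this form. The two groupings conflict on where PLHIV belong, and the one that drives sampling pools them with professionals. As written, the number of PLHIV is uncontrolled, and the cut-off of 4 applied to a pooled mean can mask opposite ratings.

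The size depends on a share that the documents do not give: about 13 to 64 PLHIV for 10% to 50% of the stratum, or about ±27 to ±12 percentage points for a proportion near 50%. The item means in the examples are illustrations. They show that masking can happen, not that it will. The correction should be made before survey quotas are set. It does not call the overall sample size into question, and it does not make four equal strata the only acceptable design. The experience requirement is a secondary matter of clarification.

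**What to change.** Within the same n = 385:

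1. Record PLHIV status for every respondent, including those who declare policy or research as their primary group.
2. Split the practice stratum into PLHIV and practice professionals, and state a minimum number of PLHIV. A fourth equal stratum of about 96 is one option; a smaller stated minimum inside the present stratum is another.
3. Report each item's rating and its importance classification separately for PLHIV.
4. Make the Abstract's groups match those in the Inclusion criteria and in both sampling sections.
5. State how the five-year experience requirement applies to PLHIV.

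**Cost.** No increase in total n. More effort is needed to recruit PLHIV, and there may be fewer professionals in practice. With four equal strata, the policy and research margins widen from ±8.7 to ±10.0 points, and practice professionals also stand at ±10.0. If PLHIV would otherwise have been about 32, reaching 96 means recruiting three times as many, so the minimum should be set with the patient organizations' likely yield in mind. The remaining changes are wording and one survey question.
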